#### **5. Participating subjects**

##### **5.1. Subject number**

The sample size estimation is based the correlation study. It is assumed that a correlation of at least 0.35 would be sufficient to use urinary total p-ABG or FIGLU as markers for

folate status. To detect such a correlation as statistically significant with a power 80% and  $\alpha$  of 0.05 samples from 49 subjects have to be analyzed (Uitenbroek, Daan G, Binomial. SISA. 1997. <http://www.quantitativeskills.com/sisa/distributions/binomial.htm>. (1 Jan. 2004). Thus, 50 subjects will be enrolled into the correlation study and from these participants for the intervention study will be selected.

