## 9. Data management and biometrical evaluation

All clinical data will be recorded in specifically prepared forms to be incorporated later into an electronic database. In the database they will be combined with the results of the laboratory analyses.

For all quantitative parameters determined a test for normal distribution will be performed according to Kolmogorov-Smirnov. If normal distribution can be assumed, mean and standard deviation will be given for these parameters. For non normally distributed data median and interquartile range will be provided and data will be transformed appropriately prior to statistical analysis.

The repeated basal determination of blood markers of folate status is performed, as it is reasoned that both parameters undergo not only random variation, but there might be trends over time, after changes of dietary habits or physiological status. The effect of these trends should be attenuated by application of the average values of two measurements taken at different time points. This should become obvious from a better correlation of the averaged values compared to the individual values. A similar reasoning is behind the complete 24h urine collection, if there are short term variations in urinary concentration of total p-ABG or FIGLU extrapolation to total volume of excretion during 24 hours via urinary creatinine concentration is not adequate. If this is the case, there should be a closer relationship between the measured 24 h excretion of p-ABG and FIGLU with RBC folate than between the 24 h excretion estimated from the spot urine sample and RBC folate.

The major focus of statistical evaluation is a correlation and receiver operator characteristics (ROC) (Streiner et al, 2007) analysis between the determined circulating folate status markers and the urinary markers of folate status. Correlation analysis will be performed according to Pearson or Spearman. For ROC analysis classification into the lowest quartile as assessed with RBC folate will be set as "Gold Standard". Corresponding specificity, sensitivity, positive predictive value and negative predictive value will be determined for urinary total p-ABG and FIGLU excretion (measured and estimated 24 h excretion). Parameters will be compared in respect to the area under the ROC curve.

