## **10. Ethical consideration, safety and insurance**

The major aim of the study is to evaluate a non invasive measure of folate status, which is applicable in children and large epidemiological trials. Although theoretical considerations and study results point towards the usability of urinary total p-ABG and FIGLU excretion as folate status markers, its application in subjects on habitual and variable diets has to be tested . Furthermore, it is important to establish the indicative value of spot urine samples, as 24h urine collections seem not possible in screening studies. According to the best of our knowledge, it has not been tried before to establish the correlation of urinary markers and blood folate markers in healthy adult males on habitual diet and free choice to consume folic acid supplements. Establishment of the correlation between the established marker and a newly proposed marker, as well as the establishment of cut-off values for the new marker, are mandatory before the application of the new marker as a screening tool in a study, which aims to identify subjects with marginal folate status. The follow up of the changes of these markers after introduction of folate supplementation is a possibility of external validation of the marker, might establish upper limits of folate status for its applicability and tests its suitability as analytical parameter in clinical studies. Thus, the proposed protocol has the potential to collect valuable scientific data and achieve progress in nutritional science.

On the other hand risk and burden for the participating volunteers are limited. The risk associated with blood sampling is marginal and urine collection is cumbersome and inconvenient, but without risk. As vitamin B12 status of the subjects is continuously monitored and deficient subjects are excluded the additional intake of 400 µg folic acid daily can be considered as safe.

In conclusion, we predict that the data obtained from this study valuably contribute to the improvement of nutritional science without significant risk for the subjects and thus the study seems ethically well justified. The study will be conducted according to the established regulations including the registration of clinical trials, the coverage by an appropriate insurance and reporting of the results in a scientific publication.

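### The ROC gold standard is this sample's own lowest RBC-folate quartile, so it tests ranking among these 50 men and its PPV and NPV do not carry over to screening for marginal folate status

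*Protocol*

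**What the plan says.** Section 9 makes correlation and ROC analysis the main focus of the evaluation. For the ROC part: "For ROC analysis classification into the lowest quartile as assessed with RBC folate will be set as" the gold standard. It continues: "Corresponding specificity, sensitivity, positive predictive value and negative predictive value will be determined for urinary total p-ABG and FIGLU excretion", for both measured and estimated 24-hour excretion. Between markers, "Parameters will be compared in respect to the area under the ROC curve".

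The sample is fixed in section 5.1: "50 subjects will be enrolled into the correlation study and from these participants for the intervention study will be selected". Section 5.2 admits apparently healthy men aged 18 to 45 with normal blood tests and adequate vitamin B12. It deliberately allows supplement users so as to widen the folate range, and it sets no folate criterion. The protocol names no absolute RBC-folate limit.

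Section 10 gives the purpose. Correlation with the established marker and "establishment of cut-off values for the new marker, are mandatory before the application of the new marker as a screening tool" in a study looking for people with marginal folate status.

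**The concern.** A quartile of the study's own sample is a relative definition. The lowest quarter of the men are cases even if all 50 are folate-replete, and only a quarter are cases even if many more have low folate. Two consequences follow.

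- The reference condition is not the one that section 10 wants to screen for. Separating the lowest quarter of these men from the rest is a statement about ranking.
- The share of cases is set by the definition and not by any population. PPV and NPV depend directly on that share, so the values that section 9 requires describe no population in which the marker would be used.

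At stake is the reading of the ROC results. A PPV taken straight from this table and quoted as a screening property would mislead wherever low folate status is rarer than one in four.

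**Working it through.** **The plan's own figure.** The only sample-size calculation concerns correlation. Section 5.1 takes r = 0.35, power 80% and alpha 0.05, and arrives at 49. Fisher's z gives n = ((z_alpha + z_power)/atanh(r))² + 3. With one-sided alpha this is ((1.645 + 0.842)/0.365)² + 3 = 49.3, which matches 49. With two-sided alpha it is 61.8. That is a separate matter; here it matters only that nothing was sized for the ROC analysis.

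**Inputs.** N = 50 and r = 0.35 come from section 5.1, and the quartile definition from section 9. My assumptions are a bivariate normal distribution, a marker oriented so that low values point to low folate, the lowest quarter of the marker called positive, and target prevalences of 2% to 25%.

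**Cases.** 50 × 0.25 = 12.5, so there are 12 or 13 cases and 37 or 38 non-cases. Prevalence is 12/50 = 24% or 13/50 = 26%.

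**Sensitivity and specificity.** The bivariate normal probability that folate and marker are both in their lowest quarter, at r = 0.35, is 0.1011.

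- Sensitivity = 0.1011/0.25 = 0.404.
- Specificity = 1 − (0.25 − 0.1011)/0.75 = 0.801.

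**PPV and NPV by prevalence p.** PPV = se·p / (se·p + (1 − sp)(1 − p)) and NPV = sp(1 − p) / (sp(1 − p) + (1 − se)p). For example, PPV at 10% is 0.0404/(0.0404 + 0.199 × 0.90) = 0.184.

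Carrying the quartile-based sensitivity and specificity to a rarer condition is itself an approximation. As a check, I redefined cases as the lowest 10%, 5% or 2% of RBC folate. A quarter of men are still called positive, so PPV = se·p/0.25.

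| Prevalence (assumed) | PPV, quartile se/sp | NPV, quartile se/sp | se / sp, cases redefined | PPV, cases redefined |
|---|---|---|---|---|
| 25% | 40.4% | 80.1% | 40.4% / 80.1% | 40.4% |
| 10% | 18.4% | 92.4% | 47.4% / 77.5% | 19.0% |
| 5% | 9.7% | 96.2% | 52.0% / 76.4% | 10.4% |
| 2% | 4.0% | 98.5% | 57.2% / 75.7% | 4.6% |

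The two PPV columns nearly agree. Simulating the first three rows gives 41%, 19% and 10%.

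**AUC.** The true AUC at r = 0.35 is 0.67, and the mean AUC over simulated samples of 50 is 0.666 against 0.668 true, so there is no inflation. For 12 cases and 38 non-cases the Hanley–McNeil standard error at 0.67 is 0.095, giving 0.67 ± 1.96 × 0.095 = 0.48 to 0.86. An observed sensitivity of 10/12 has an exact 95% interval of 52% to 98%.

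**If the cut-off is chosen on the same 50 men** (not stated in the protocol). I took the cut-off with the largest Youden index in each of 10,000 simulated samples at r = 0.35. Apparent sensitivity and specificity average 0.725 and 0.649, so J = 0.725 + 0.649 − 1 = 0.37. The same cut-offs truly achieve 0.591 and 0.619, so J = 0.21.

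**The case against.** Several points on the other side are sound.

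- **The ROC figures do not decide the study.** Section 9 makes the obtained coefficients the primary criterion of applicability, and the hypotheses in section 4 concern correlation and response to supplementation. This stands and limits the consequence. Even so, predictive values can come only from the ROC part, and section 10 ties screening use to cut-offs.
- **Screening performance is not overstated across the board.** A reader might infer that it is. AUC is unbiased. NPV is understated at lower prevalence. When cases are redefined as more extreme low folate, AUC rises from 0.67 to 0.69, 0.71 and 0.735 at 10%, 5% and 2%, and sensitivity rises as well. Only PPV is clearly flattered, and only if target prevalence is below 25%, a figure the protocol does not give.
- **The sample may contain men with marginal status.** A reader might infer that none of these healthy men is folate-marginal. The protocol does not support that: it sets no folate criterion and aims for a wide range, so the number is unknown.
- **Same-data cut-off selection is an inference.** Section 9 states no cut-off rule. Because these 50 men are the only sample, and the follow-up that section 10 calls external validation uses men drawn from them, the inference is natural. A rule, confidence intervals or optimism correction may still sit in an analysis plan that is not shown, so their absence here is not a fault. Specificity, in any case, rests on the 37 or 38 non-cases.

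None of this touches the core point: the relative gold standard and the request for PPV and NPV from it are fixed in section 9 itself.

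**Conclusion.** The concern holds in this form. As defined, the ROC analysis measures ranking within this sample, and the PPV and NPV required by section 9 reflect a share of cases of 24% to 26% set by the definition. At r = 0.35, PPV falls from about 40% at 25% prevalence to 18–19% at 10% and about 10% at 5%, while NPV rises from about 80% to 92–96%. These figures rest on bivariate normality, a positive call for the lowest quarter of the marker, and assumed prevalences.

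AUC is imprecise but not biased. Optimism in sensitivity and specificity (J of 0.37 apparent against 0.21 true) arises only if the cut-off is picked on these data by the Youden index, which the protocol does not say. The correlation objective is unaffected. This is a worthwhile, inexpensive correction to how the screening results are defined and reported.

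**What to change.** Amend section 9 as follows.

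1. Replace raw PPV and NPV with values calculated from sensitivity and specificity over a stated prevalence range, for example 2% to 25%, noting that sensitivity and specificity come from the quartile definition.
2. Keep the quartile analysis but label it as ranking within the sample. Add, as a secondary reference, an absolute RBC-folate limit named before results are seen (the laboratory's reference limit), and report how many men fall below it.
3. If few men fall below that limit, make no claim about detecting marginal status and call any urinary cut-off provisional. If a cut-off is chosen on these data, report its optimism-corrected performance, for example by bootstrap.

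The cost is a little extra analysis on data already being collected, with no further subjects, samples or assays. The reported figures will look less favourable, and there may be too few men below the absolute limit for a separate ROC analysis.

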#### **4. Objectives**

The major objective of the proposed study is to demonstrate the suitability of new markers for folate status in humans, which avoid blood sampling, as required for the established marker RBC folate concentration, but can be obtained from spot urine samples.

Specific hypotheses to be tested:

Correlation study:

- a) The 24 h urinary excretion of total p-ABG, as extrapolated via urinary creatinine concentration from the total p-ABG concentration in a spot sample is significantly correlated to RBC and plasma folate levels in the studied subjects
- b) The 24 h urinary excretion of FIGLU, as extrapolated via urinary creatinine concentration from the FIGLU concentration in a spot sample is significantly correlated to RBC and plasma folate levels in the studied subjects

Intervention study:

- a) changes in folate status (RBC folate) after supplementary intake of folate result in increased urinary excretion of total p-ABG and FIGLU in subjects identified with a low folate status and in subjects identified with a high folate status among the study participants of the correlation study

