## 6.2 Intervention study

The part of the study described so far (correlation study) relates to the evaluation of the principal relationship between urinary excretion of total p-ABG and FIGLU and blood markers of folate status, which is needed for the evaluation of the suitability of these markers as screening tools and as proxies for folate status. The second part (intervention study) shall clarify, whether total p-ABG and FIGLU excretion are suitable for the determination of changes in folate status after increased intake of folic acid starting from relatively high or low levels.

From those subjects, who do not already take supplements, 15 persons each from the highest and lowest quartile in respect to RBC folate status (based on RBC folate concentration at the first appointment) will be asked to participate in a 12 week supplementation study. The participating subjects will be given a folate supplement, providing 400 µg of folic acid per day. For the evaluation of the time course of the blood and urine markers of folate status after 6 weeks and after 12 weeks blood and urine samples will be obtained. During the intervention period subjects will be contacted by telephone regularly to discuss questions and to enhance adherence to the protocol.

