### 1. Second appointment (continued):

- subjects (n=20, 10 each for the highest and lowest quartile of RBC folate status) who participate in the intervention study will be given a pack with 50 tablets (400 µg folate/tablet) of a commercially available folate supplement
- a brief questionnaire to note any unusual events or complaints will be provided
- container (2.0 l, Sarstedt 77.580, containing 5 g ascorbate to prevent folate breakdown) and instructions for 24h urine collection will be handed over to the subject (if collection of spot samples is found useful in the correlation study spot samples will be collected instead of the 24h urine)
- a third appointment about 6 weeks later will be scheduled

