The obtained coefficients are the primary criterion for the applicability of the latter parameters as indicators of the subjects folate status. For a more detailed analysis of the data multiple regression analysis with RBC folate as the independent parameter and urinary excretion of total p-ABG or FIGLU as dependent variable including correction for other potentially confounding factors (e.g. vitamin B12, vitamin B6, age) will be performed. For these detailed analyses the support of an experienced biostatistician will be sought.

For evaluation of the time course of blood and urine markers of folate status repeated measures analysis of variance will be performed, with group allocation (high or low folate status according to RBC folate) as an independent factor. Furthermore, correlation analysis as described for the basal values will be performed, to investigate the suitability of urinary folate markers under conditions of a defined recent change of folate intake.

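### The follow-up correlation in 20 men taken from the two ends of RBC folate depends on that selection and does not show whether urinary markers track individual change in folate status

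*Protocol*

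**What the plan says.** Section 6.2 asks whether total p-ABG and FIGLU excretion are "suitable for the determination of changes in folate status after increased intake of folic acid", starting from high or low levels. The intervention hypothesis in section 4 reads "changes in folate status (RBC folate) after supplementary intake of folate result in increased urinary excretion", in both low-status and high-status men. Those treated are "subjects (n=20, 10 each for the highest and lowest quartile of RBC folate status"). They are chosen on RBC folate at the first appointment and only among men not already taking supplements.

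Section 9 plans two analyses for this part. One is a repeated measures ANOVA of the blood and urine markers over time, with high or low group as factor. The other is in the next sentence: "correlation analysis as described for the basal values will be performed, to investigate the suitability of urinary folate markers" when folate intake has recently changed by a known amount. The basal analysis it refers to is a Pearson or Spearman correlation between circulating and urinary markers.

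Section 5.1 gives the only benchmark for a correlation: "It is assumed that a correlation of at least 0.35 would be sufficient". It ties the calculation to the first part of the study: "The sample size estimation is based the correlation study".

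**The concern.** There are two difficulties with the follow-up coefficient.

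- **Selection.** Taking both ends of RBC folate changes its spread, and a correlation coefficient, unlike a regression slope, moves with that spread. The value from these 20 men is not on the same scale as the value from the 50.
- **Question.** The intervention part is about change. A correlation of levels at week 6 or 12 still carries the association that existed before the first tablet.

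A sizeable follow-up r could then be read as evidence that urinary markers follow a change in status when it mainly restates the starting contrast. Section 10 presents the follow-up of these markers as a possible external validation, so the coefficient is likely to be given weight.

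**Working it through.** **1. The plan's own figure.** Inputs from section 5.1: r = 0.35, power 80%, alpha 0.05, 49 subjects. By Fisher's z, n = ((z_alpha + z_power)/atanh(r))² + 3, with atanh(0.35) = 0.3654.

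- One-sided: ((1.645 + 0.842)/0.3654)² + 3 = 49.3, which agrees with the stated 49.
- Two-sided: ((1.960 + 0.842)/0.3654)² + 3 = 61.8. This is a separate matter, not pursued here.

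The calculation concerns an unselected sample. There is none for the 20 men.

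**2. Effect of selection alone.** For a normal variable restricted to its two outer quartiles, the variance is multiplied by v = 1 + q·φ(q)/0.25. With q = 0.674, v = 1.857. Then r_sel = r·√v / √(1 + r²(v − 1)).

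- r = 0.20 becomes 0.27.
- r = 0.35 becomes 0.35 × 1.363 / √1.105 = 0.45.
- r = 0.50 becomes 0.62.

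Simulating 50 men, with 10 drawn from each outer 13, gives 0.26 to 0.27, 0.44 to 0.45 and 0.61.

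**3. What can offset it.** Supplement users may be among the 50 but not among the 20. The protocol gives no figures for them. Assume 20 to 30% users, RBC folate 1.5 to 2.5 SD higher in users, quartiles formed among non-users, and reliability 0.8. The RBC folate variance in the 20 relative to the 50 then falls from 1.60 (no users) to between about 1.17 and 0.71. With a true r of 0.35, observed as 0.31 in the 50, the selected r is about 0.34 down to 0.23, against 0.41 without users. The direction relative to the 50-man r is therefore not fixed.

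**4. What the follow-up coefficient contains.** Write follow-up as baseline plus change, X + ΔX for RBC folate and P + ΔP for the urinary marker. The covariance at follow-up is Cov(X,P) + Cov(X,ΔP) + Cov(ΔX,P) + Cov(ΔX,ΔP). The first term existed before supplementation, and only the last is tracking of change. Adding the same amount to every man's marker leaves r unchanged, so r cannot distinguish a uniform rise from none.

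**5. Size of this.** Simulation with basal r = 0.35. Assumptions not in the protocol: reliability 0.8 to 1.0, SD of individual RBC change 0.5 baseline SD, marker change independent of RBC change.

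| Baseline differences kept | Level r, 20 selected | Level r, unselected men | Change-on-change r |
|---|---|---|---|
| 100% | 0.40 | 0.30 to 0.31 | about 0 |
| 50% | 0.31 to 0.35 | 0.21 to 0.24 | about 0 |
| 25% | 0.19 to 0.25 | 0.12 to 0.15 | about 0 |

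The level correlation is positive throughout although the marker does not follow individual change. In these settings, which contain no supplement users, it stays above that of unselected men, but it can fall below the basal 0.35.

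**6. Precision of the alternative.** With n = 20 and r = 0.35, the 95% CI is tanh(0.3654 ± 1.96/√17) = -0.11 to 0.69. Two-sided power is 33%, and the smallest r detectable with 80% power is 0.59.

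**The case against.** The strongest reply is that the protocol does test change. The repeated measures ANOVA examines mean response over time by group, which is a fair reading of the section 4 hypothesis. The correlation is a supplement with its own purpose: whether urinary markers still indicate status after a recent change in intake, which is a question about levels. This stands as far as it goes. But the ANOVA treats each marker's mean course separately, and even for the question about levels a coefficient from a sample chosen on RBC folate needs adjustment or a caveat.

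A reader might infer that a marker with no response to supplementation could pass the study. The protocol does not support that: such a marker would show no time effect in the ANOVA, 0.35 appears only in the sample size section, and nothing applies it to the 20 men.

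A reader might also infer that r is always inflated relative to the 50-man value. Steps 3 and 5 show that it need not be. Nor should the greater chance of seeing r ≥ 0.35 be put down to selection alone. With a true r of 0.25 that chance is about 23% in 50 men, already 30 to 34% in 20 unselected men, and 47 to 50% in the selected 20.

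Finally, the detail could be left to a statistical analysis plan. However, the protocol already names the analysis and its sample, so the point concerns what is stated, not what is missing.

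**Conclusion.** The point holds in limited form. The follow-up level correlation depends on how the 20 men were chosen and largely carries the pre-existing high-low difference, so it does not show whether urinary markers track individual change. No planned analysis links a man's urinary change to his RBC or serum folate change.

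The shift from 0.35 to about 0.45 assumes normal data and nothing else changing. Its size, and even its direction relative to the 50-man r, depend on the exclusion of supplement users and on convergence of the groups, neither of which the protocol quantifies. The argument in step 4 does not depend on these assumptions. The 50-man correlation analysis is unaffected. This is a worthwhile, inexpensive improvement to the intervention part, not a flaw in the study's main result.

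**What to change.** In section 9:

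- Replace the sentence on follow-up correlation with a within-subject analysis. Either correlate each man's change in RBC and serum folate with his change in total p-ABG and FIGLU, from appointment 2 to weeks 6 and 12, or use a repeated-measures correlation or a mixed model with group as covariate. Report the estimate with its 95% CI, not as a pass or fail test.
- Keep the repeated measures ANOVA as the test of mean response by group.
- Present any level correlation at weeks 6 and 12 as group-adjusted and from a selected sample, and state that it is not to be compared with the 50-man r or with 0.35.

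No new samples are needed. Blood and urine are already taken at appointments 2, 3 and 4. Appointment 2 provides both a 24-h collection and a spot sample, so changes can be formed on one type of urine sample whichever is used later. The cost is rewording and a coefficient that will probably be smaller and will be imprecise, with an interval of about -0.11 to 0.69 around 0.35.
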